### Interventions

2.5

The research team formed a multidisciplinary team consisting of a thyroid cancer pharmacist, a nursing specialist, a thyroid cancer physician, and a public health specialist to discuss and develop the intervention program. The control group received routine medical and nursing care, and the intervention group received the MTM-based mHealth intervention in addition to routine medical care.

#### Intervention group: online MTM-based health education

2.5.1

The intervention group receives MTM-mHealth, and the realization of health education will rely on the smart terminal WeChat platform. Combined with the chat communication function of WeChat, timely communication between physicians and patients will be realized, and patients’ concerns will be answered by physicians or professional nurses in a timely manner. At the same time, through the WeChat platform, physicians or professional nurses can realize timely interventions for patients, including daily reminders of medication taking, popularization of thyroid cancer-related science, and interpretation of cutting-edge research on thyroid cancer.

The intervention group had WeChat group health education, online health education lectures, received routine medical care such as health education program and medication supervision on the day of hospitalization, then received treatment in the outpatient clinic, and received intervention in mobile health education after discharge for 3 months, and the content of the intervention was designed based on the theory of MTM, and the flowchart is shown in Figure 2.

##### Participatory dialog (when strengths outweigh weaknesses)

2.5.1.1

Purpose: to motivate patients to start behavioral change, so that patients produce initial action self-efficacy.

Measures: Give each patient a copy of the booklet “Health Education for Thyroid Cancer Patients.” While distributing the education booklet, the physician explains and emphasizes the common problems of the patients, encourages the patients to face the disease positively, and guides the patients to consciously improve their own health behaviors. During the first visit, patients and physicians ask each other questions as much as possible, encouraging patients to actively participate in the initial patient-physician communication. At the same time, the physician added the patient’s WeChat contact information, in order to further provide timely health education to the patient.

After the patient is discharged from the hospital, the physician and the patient regularly communicate with each other through the online doctor-patient salon at 9:00 a.m. on Saturdays, the content of the communication includes disease cognition, prognosis and development, etc., and the link includes the physician’s explanation, the physician-patient Q&A, and the patient–patient communication, etc., and the physician needs to guide the patient to explore the advantages and disadvantages of improving the self-health behaviors on the recovery of the disease, and the physician needs to emphasize that the advantages of the self-health behaviors outweigh the disadvantages so that the patient The physician should emphasize that the advantages of self-health behaviors outweigh the disadvantages, so that the patient can actively participate in the joint decision-making process.

##### Behavioral confidence (belief in one’s ability to achieve desired behaviors)

2.5.1.2

Purpose: to enhance patients’ confidence in changing health behaviors in the future.

Measures: Physicians and relevant nursing staff set up a doctor-patient exchange group on WeChat, grouping patients according to the initial treatment ward and electing a group leader, who organizes regular exchanges between patients, with the group leader deciding the time of exchanges himself/herself. Physicians and related nursing staff encouraged and instructed all patients to fill out a “health behavior diary” to record the daily maintenance of health behaviors and problems and experiences encountered during the process, and to share and exchange them in the WeChat group every day. At the same time, patients were encouraged to communicate with their physicians in a timely manner, and the physicians evaluated the progress of the patients’ health behaviors in a timely manner. With half a month as a cycle, physicians or relevant nursing staff after evaluation and comparison, the merit of inviting patients who maintain good health behavior to present themselves, in the form of WeChat group to open a patients’ club, the patients through the group learning and communication, sharing daily experience, discussion, interaction and mutual learning.

##### Changes In The physical environment (environments that enable behavior)

2.5.1.3

Purpose: Provide patients with educational resources in an online format to make resources that support patient health behavior change more accessible.

Measures: Physicians as well as relevant nursing staff need to emphasize with patients and their families at the time of patient discharge and during online communication that common salt should be used to replace iodized salt as much as possible in daily life, educate patients to control the intake of iodine-containing foods, avoid high iodine diets, such as seaweeds like kelp, seaweed and sea fish, and refrain from drinking stimulating beverages such as coffee, strong tea, and cola, and that they should be given diets that are high in calories and contain sugar, proteins, and B-vitamins.

Based on the “Health Education for Thyroid Cancer Patients” manual, physicians and related nursing staff will independently design a delivery program for educational materials, which will be based on an independently constructed multimedia database, and the health education materials in the multimedia database will be evaluated and screened by several related experts before inclusion. The push program will take every 3 days as a push cycle, and push three or more pieces of thyroid cancer related educational materials to patients, which will include video, graphics, voice explanations, etc. The content will include popularized articles about the disease process, interspersed with relevant information about the past cases, the danger of thyroid cancer, and the adverse outcomes of the later stages of the development of thyroid cancer, etc. Physicians can cooperate with the related materials to explain the health behavior. Physicians can explain the necessity and effect of healthy behaviors to improve the adverse outcomes, and guide patients to establish risk awareness. Nursing staff will encourage patients to punch cards in the WeChat group every day, so that they can effectively read the relevant popular science articles.

##### Emotional transformation (intention to overcome self-doubt)

2.5.1.4

Purpose: To guide the patient’s feelings and emotions to focus on changes in health behaviors, and to guide thoughts to maintain such changes.

Measures: Physicians or relevant nursing staff will remind patients of the health behaviors they need to pay attention to in their lives on the WeChat platform at 9:00 p.m. every day. Relevant texts will be edited in advance and archived in the missionary material push plan, and reminders will be given according to the relevant plan. Physicians encourage and help patients to develop long-term health behavior improvement plans. For those with low adherence: focus on behavioral reinforcement and supervision, repeatedly emphasizing to patients the dangers of thyroid cancer and the benefits of maintaining healthy behaviors, the benefits of taking medication on time, etc.; for those with intermediate levels: focus on praise and encouragement to help them maintain confidence; for those with high levels: focus on monitoring. Physicians need to take the initiative to solicit the recovery effect of all patients, guide patients to take levothyroxine sodium tablets accurately, inform patients of the precautions to be taken after radioactive iodine-131 treatment in a timely manner, and in response to the adverse reactions of the patients after radioactive iodine-131 treatment, patients should be pacified in a timely manner and encouraged to cooperate with the treatment positively.

If patients have negative emotions, resist or discontinue health behaviors during treatment, physicians should promptly analyze the reasons for the discontinuation of their behaviors, take corresponding measures, and guide patients to carry out self-regulation, so that they can quickly resume healthy behaviors despite the discontinuation of their behaviors in a timely manner.

##### Practice change (assessing and adjusting efforts to achieve desired behaviors)

2.5.1.5

Purpose: To guide the patient in reflective action and make the patient think about the impact of his or her health behavior change.

Measures: The physician regularly organizes a patient exchange salon on Saturday mornings at 9:00 a.m. every week, where patients share their “health behavior diaries” with each other, the daily maintenance of health behaviors and the problems encountered during the process, experiences, etc. For those with low compliance: focusing on the reinforcement of behaviors and urging, the physician needs to discuss the reasons with the patient and help him or her to find a specific solution. For those with low adherence: focus on behavior reinforcement and supervision, the physician needs to discuss the reasons with the patient and help him/her find specific solutions, and emphasize to the patient the disadvantages of abandoning the maintenance of healthy behaviors; for those with medium level of adherence: focus on praise and encouragement, and help him/her maintain confidence; for those with high level of adherence: focus on monitoring.

##### Social environment change (using positive relationships to achieve desired behaviors)

2.5.1.6

Purpose: construct timely incentives for patients to change health behaviors.

Measures: Physicians and patients communicate with each other in a timely manner on the WeChat platform to understand their psychological state, and combine psychological massage method, verbal appeasement method, and distraction method to motivate patients to make changes and alleviate their poor psychological state through good cases. For those who maintain good health behaviors, timely encouragement is provided in the WeChat group; for those who maintain poor health behaviors, physicians need to communicate with them on a one-to-one basis in a timely manner, take appropriate measures, and guide the patients to self-regulation, so that they can quickly restore healthy behaviors even in the event of behavioral interruptions in a timely manner.

#### Control group: routine care

2.5.2

Routine discharge education will be given to the control group at the time of discharge, and patients will be given a booklet entitled “Health Education for Patients with Thyroid Cancer,” which includes basic knowledge of thyroid cancer and lifestyle guidance, such as rational diet, medication guidance and adverse reactions. Regular telephone follow-up will be given to the patients, the first telephone follow-up will be given at the end of the first month after discharge and monthly thereafter.

### Collection and screening of health education materials

2.6

#### Sources of health education materials

2.6.1

The educational materials used for health education come from the Internet, including videos and illustrations. The illustrations come from WeChat, Wikipedia, doctor’s Q&A, or domestic and international databases such as CNKI, and the videos come from WeChat, Wikipedia, doctor’s Q&A, etc. The cases come from Baidu documents or literature. The case information was obtained from Baidu documents or literature, and the educational materials used should be scientific and have corresponding references.

#### Screening of health education materials

2.6.2

After centralizing all the health education materials, they will be sent for external review to the experts in thyroid cancer related fields, who will evaluate the materials according to the thyroid cancer expert evaluation form. After the experts return the evaluation opinions, they will centralize the screening of the quality health education materials, and the selected health education materials will be used as the push database of the health education materials. The push database will contain article titles, related links, corresponding sources, corresponding material types, etc. The materials will be categorized according to their corresponding contents. The materials will be categorized into disease awareness, postoperative care, diet, exercise, and other sections according to their corresponding content, so as to facilitate the formulation of a corresponding delivery plan for patients.

### Outcomes

2.7

Primary Outcome: Change in TSH from Baseline and at 3 and 6 Months Follow-Up.

Secondary outcomes:

changes in self-management behaviors: changes measured by the MTM Theory Scale, changes in frequency of iodine-containing diets, medication adherence.Social cognitive and psychological: quality of life, satisfaction, depression, anxiety and fear of cancer recurrence.Metabolic control: thyroxine (T4), triiodothyronine (T3), FT3, FT4.

The corresponding study questionnaires completed by all patients at baseline as well as at follow-up were piggybacked on a web-based platform (Questionnaire Star). Clinical pharmacists distributed the questionnaires via Questionnaire Star, and patients were instructed to fill them out by pharmacists either face-to-face (during hospitalization) or by telephone (after discharge). Patient demographic information was collected through the case system and self-designed questionnaires.

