**Methods:**

This research project is a quantitative methodological study, and the trial will be a single-blind, single-center randomized controlled trial conducted at the Fourth Hospital of Harbin Medical University in Harbin, Heilongjiang Province. The study subjects are patients over 18 years of age with differentiated thyroid cancer who were given radioactive iodine-131 therapy as well as endocrine therapy after radical surgery for thyroid cancer. The intervention group will receive MTM-mhealth, and the realization of health education will rely on the smart terminal WeChat platform. Routine discharge education will be given to the control group at discharge. The primary outcome will be change in thyroid-stimulating hormone (TSH) from baseline and at 3 and 6 months of follow-up, and secondary outcomes will include change in self-management behavior, social cognitive and psychological, and metabolic control.

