### Sample size

2.3

This study is a randomized controlled trial, the intervention group is the mHealth intervention group and the control group is the usual care group, the achievement rate of TSH in the study population is the main outcome indicator observed, and the patients’ TSH level control ﹤0.1 mU/L will be completed to achieve the standard. Based on the review of the literature, it is expected that the achievement rate of the mHealth intervention group is 90%, and the achievement rate of the control group is 60%. Setting bilateral *α* = 0.05, the degree of certainty was 90%. Using the PASS15 software, we obtained a sample size of N1 = 39 cases for the treatment group and N2 = 39 cases for the control group, and taking into account the loss of visits and refusal of visits by 20%, the final minimum number of subjects needed for the intervention group and the control group was 49 cases each, for a total of at least 98 subjects to be included in the study.

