### Treatment programs

2.4

Patients in both groups will receive administration of iodine 131 therapy combined with thyroid hormone replacement therapy (53, 54). Prior to receiving iodine 131 therapy, patients will be required to undergo a thyroid uptake scan to determine if there is any residual or recurrent thyroid cancer (55). Depending on individual circumstances, patients are administered iodine 131 between 50 and 200 meters Curie (mCi) in a separate isolation room within the hospital. After administration, patients are hospitalized in an isolation room for 3 days to minimize radiation hazards, and are kept away from pregnant women and small children, avoiding close contact with other people, etc., to ensure safety. After iodine 131 treatment, start to take oral levothyroxine sodium tablets on the second natural day, generally the initial dose is 50 μg per day, the maximum amount does not exceed 100 μg, and the maintenance dose is 50–200 μg per day. Four weeks later, review the thyroid function index, and according to the results of the test, the dose will be maintained or adjusted. Therapeutic target: TSH 0.3 ~ 0.5 mU/L, free thyroxine (FT4) 10.3 ~ 25.8 pmol/L, free triiodothyronine (FT3) 2.16 ~ 6.78 pmol/L.

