### Variables measurement

2.8

Socio-demographic variables will be collected: gender, age, education, usual residence, *per capita* monthly income of the family, mode of bearing medical expenses, and clinical information such as duration of DTC, detailed medical history.

Physiological Indicator Variables: TSH will be detected using radioimmunoassay (RIA), the medical staff will clean the patient’s blood collection site using a sterilized cotton ball, and then use a needle to take an appropriate amount of fasting venous blood 5 mL, centrifuged at 3000 r/min for 5 min, serum will be separated, and a certain amount of TSH antibody labeled with the radioisotope iodine-125 will be added to the processed serum to bind to the TSH to be detected. TSH. Using biochemical techniques, the antibody-bound TSH and unbound free TSH were separated into solid phase and free phase. The radioisotopes in the solid phase are measured to obtain a corresponding count value, from which the concentration of TSH in the sample can be determined. Based on the stratification of risk factors for recurrence of differentiated thyroid cancer, patients can be categorized into low-risk, intermediate-risk, and high-risk strata, and postoperative serum TSH target values are set accordingly (56). In general, the division is based on factors such as age, gender, tumor stage, presence of lymph node metastasis, and type of thyroid cancer variant. All patients included in this trial were high-risk patients treated with iodine 131, and according to treatment guidelines, for high-risk patients, postoperative serum TSH should be suppressed to very low levels (<0.1 mIU/L) or completely suppress thyroid function to minimize the risk of recurrence. Therefore, the TSH compliance rate was defined as postoperative serum TSH < 0.1 mU/L, and this criterion was used to calculate the TSH compliance rate.

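### The 90% power was calculated for a TSH achievement rate, but the declared primary outcome is change in TSH at two visits, for which power is not shown

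*Protocol article*

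**What the plan says.** - **Section 2.7, Outcomes:** "Primary Outcome: Change in TSH from Baseline and at 3 and 6 Months Follow-Up". The secondary outcomes are self-management, social-cognitive and psychological measures, and T4, T3, FT3 and FT4. The TSH achievement rate is in neither list.
- **Abstract, Methods:** "The primary outcome will be change in thyroid-stimulating hormone (TSH) from baseline and at 3 and 6 months of follow-up".
- **Section 2.3, Sample size:** "the achievement rate of TSH in the study population is the main outcome indicator observed", with success at TSH below 0.1 mU/L. It expects 90% success on the intervention and 60% on control, at two-sided alpha 0.05 and 90% power. This gives 39 per arm, 49 per arm after 20% loss, and 98 in total. No time point is attached to the rate.
- **Section 2.8, Variables measurement:** "the TSH compliance rate was defined as postoperative serum TSH < 0.1 mU/L", again without a visit.
- **Section 2.4, Treatment programs:** the therapeutic target for TSH is 0.3 to 0.5 mU/L.
- **Section 3, Statistical analysis:** each test is two-sided at p < 0.05. The Mann–Whitney test is assigned to scale scores. No test is named for TSH, either as a change or as a rate.

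**The concern.** The article names two different main outcomes. One is binary, has a sample size and is missing from the outcome list. The other is continuous, is declared primary and has no sample size. A reader of the results could not tell which comparison was confirmatory, and the 90% power would be credited to an outcome for which it was never calculated.

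The declared primary also covers two visits without ranking them. The intervention lasts 3 months (Section 2.1), so the 3-month visit measures the effect at the end of the intervention and the 6-month visit measures its persistence. These are different questions, and the article does not say which one decides the trial.

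**Working it through.** **1. Reproducing the plan's figure (inputs from Section 2.3).** Two proportions, unpooled variance:

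n = [p1(1−p1) + p2(1−p2)] × (z0.975 + z0.90)² / (p1−p2)²
= (0.09 + 0.24) × 10.507 / 0.09 = 38.5, so 39 per arm.

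Dropout: 39 / 0.80 = 48.75, so 49 per arm and 98 in total. The plan's figures are reproduced. Power at 39 per arm is 90.3% by this formula and 87.9% by the pooled-variance formula. The calculation is sound for the rate, and only for the rate.

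**2. What 39 per arm gives for a continuous change.** The smallest standardized difference in change detectable with 90% power is (z0.975 + z0.90) × √(2/39) = 0.734 SD; for 80% power it is 0.634 SD. Power at other standardized differences:

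- 0.2 SD: 14%
- 0.4 SD: 42%
- 0.6 SD: 76%
- 0.8 SD: 94%

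The article gives neither the difference nor the SD, so the trial cannot be placed on this scale.

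**3. Illustration under stated assumptions.** Assume log-normal TSH, with follow-up values giving exactly 60% and 90% below 0.1 mU/L, 39 per arm and the Mann–Whitney test. Follow-up log-SD is 1 to 2, baseline log-SD 0.5 to 1, and baseline–follow-up correlation 0 to 0.5. None of these spreads, correlations or baseline medians comes from the article. Approximate simulated power:

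- Raw change, median baseline TSH 2–60 mU/L: 4–15%
- Raw change, median baseline 0.3 mU/L: 17–83%
- Raw change, median baseline 0.1 mU/L: 54–99%
- Change on the log scale, all these baselines: 84–100%

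Raw change loses power when baseline is high and variable, because the subtraction adds baseline spread far larger than the follow-up difference. The log scale is not immune. On a normal scale the assumed rates imply a follow-up difference of z0.90 − z0.60 = 1.03 SD. If the baseline SD is two, three or five times the follow-up SD, power on change is 53–87%, 30–47% or 14–18% (correlations 0 to 0.7).

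**4. Two visits.** If either visit at p < 0.05 counted as success, the false-positive risk for independent tests would be 1 − 0.95² = 9.75%. With correlated test statistics it is 9.1%, 8.4% and 7.0% at correlations 0.5, 0.7 and 0.9.

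For comparison, testing the rate at both visits with alpha 0.025 each would need 0.33 × 12.411 / 0.09 = 45.5, so 46 per arm. After dropout that is 46 / 0.80 = 57.5, so 58 per arm and 116 in total.

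**The case against.** A condensed article may leave the test, the scale and the handling of two visits to an analysis plan that is not shown. A joint longitudinal test, a rule that both visits must succeed, or one named primary visit would not inflate the error rate, so the 7–10% is conditional. This stands. What an analysis plan cannot do is make Sections 2.3 and 2.7 both true: the article itself states two main outcomes.

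A reader might go further in four ways that the documents do not support.

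- **That the declared outcome has almost no power.** This is true only for raw change from a high baseline. On the log scale, or from a low baseline with little spread, change can match or exceed the power of the rate. At median baseline 0.3 mU/L, with baseline log-SD 0.3–0.5 and correlation 0.5, even raw change reaches 57–93%.
- **That baseline TSH is measured off hormone replacement.** Section 2.4 has patients "start to take oral levothyroxine sodium tablets on the second natural day" after iodine-131, which suggests it. But Table 2 places the sample only at month 0, and the reference to hospitalization in Section 2.7 concerns questionnaires. The inclusion criterion requiring endocrine therapy after surgery can be read as patients already on treatment.
- **That success could be claimed on any of four tests (rate or change, at either visit).** No passage proposes that scheme.
- **That the 3-month rate is what was powered.** Section 2.3 names no visit.

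**Conclusion.** The article is wrong as written. The outcome that was powered is not the declared primary and is absent from the outcome list, so the 90% power was not calculated for change in TSH and cannot be verified for it. This follows from the text alone and needs no assumption.

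The size of any power loss is undetermined. The illustrative extremes, about 4% and nearly 100%, depend on a baseline distribution and a scale that the article does not state. The absence of a primary visit is also plain on the page; the 7–10% error rate applies only if success at either visit would be enough.

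The mismatch should be settled before analysis, because it leaves the confirmatory hypothesis undefined.

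**What to change.** Make the powered quantity, the proportion of patients with TSH below the threshold, the single primary outcome in the Abstract and Section 2.7, at one named visit and with a matching test. Three months, the end of the intervention, is a natural choice, but it has to be added because Section 2.3 names no visit. Test the other visit only if the first is significant. Make continuous TSH secondary, analysed as log follow-up TSH adjusted for log baseline TSH rather than as raw change.

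This keeps 39, 49 and 98 as long as the threshold stays at 0.1 mU/L. The target of 0.3 to 0.5 mU/L in Section 2.4 conflicts with that threshold: a patient within the target would count as a failure in Sections 2.3 and 2.8. The passages must be reconciled, and if the threshold changes, the expected rates and the sample size must be rechecked.

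If the sponsor prefers to keep change in TSH as primary, it should state the scale, the expected difference, the SD and the deciding visit, and restate the power for 98 patients.

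The cost is a protocol amendment submitted to the Ethics Committee (Section 3.1.4) while recruitment, open since March 2023, is under way. One visit also loses equal standing with the other.
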